## Methods

### Participants

We will recruit implementation science experts (*n* = 30) and UCD experts (*n* = 30) to participate in this study. Expertise will be self-reported and can be based on experience in research, practice/industry, and/or education over the past 5 or more years. Our planned enrolment is twice the recommended sample size for concept mapping (*n* ≥ 15 per participant group; see [33]) to ensure that we can make meaningful comparisons between results from implementation versus UCD experts.

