### Analytic strategy

After sorting and rating are complete, the final step of concept mapping is data analysis [32]. In addition to analyses of concept mapping data, we will use software programmes such as Excel and SPSS to examine descriptive statistics (e.g. means, standard deviations, frequency counts) for demographic variables and survey responses (e.g. ratings of collaboration options). As noted previously, we will analyse data provided by all participants (including those who do not complete all study steps), which could result in uneven numbers of implementation experts versus UCD experts for certain analyses. This is not a problem in concept mapping because the technique does not rely on traditional assumptions for statistical significance and power [33].

The analytic strategy for concept mapping data requires further explanation. To start that process, we will use multidimensional scaling techniques (embedded in CSGM [37]) to identify clusters of implementation and UCD strategies that were generated most consistently across participants. CSGM will empirically generate any number of clusters that the researcher specifies, but it is up to the researcher to select the appropriate set of clusters (e.g. there is no established cut-off for minimum bridge values, which represent the closeness of relationships between concepts in a cluster, that indicate ‘good’ clusters). Consistent with the ERIC study [8], the research team will review the results for conceptual clarity and credibility before selecting which set of clusters to report in our findings. To guide that process, we will examine visual summaries of the data that can be produced in CGSM, such as cluster maps, which represent the relatedness of concepts within and between clusters in terms of visual distance and can be weighted by key dimensions (e.g. importance, feasibility), and ladder graphs, which provide a visual representation of the relationship between dimensions (e.g. importance and feasibility) within and across clusters. We will also consider the extent to which clusters are consistent with or expand upon the (1) clusters of implementation strategies identified in the ERIC study [8], (2) CFIR domains [9], and (3) the Promoting Action on Research Implementation in Health Services framework [41], which describes implementation of research evidence in practice contexts.

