After we have selected the final set of clusters, we will characterise the importance and feasibility ratings for each cluster and strategy. We will use CGSM to visually represent the relationships among concepts using go-zone graphs that plot clusters and strategies along key dimensions (e.g. plots of importance vs. feasibility). Go-zone graphs using construct means as graph axes can be used to characterise ‘Go/No-Go/Proceed-With-Caution’ zones among the four quadrants of a scatterplot; these zones will illustrate which clusters are particularly promising for future actions such as collaboration among implementation experts and UCD experts. Moreover, to promote deeper understanding of the connections between implementation and UCD, we will also explore the level of convergence (i.e. extent to which concepts represent overlap between fields) and divergence (i.e. extent to which concepts represent unique contributions from a single field) in our findings by inspecting the number and types of strategies in each cluster.

Following the aforementioned initial analyses of concept mapping data, which will examine results across rating and sorting data from all participants, we will also examine results separately for each subgroup of experts (i.e. implementation vs. UCD). Specifically, we will apply the same analytic approach described previously with data separated by professional expertise, and we will examine differences in (1) the number and contents of clusters and (2) the ratings of each cluster. Within CSGM, we will generate the same data visualisations (e.g. concept maps, ladder graphs, go-zone graphs) separately for each group. Outside of CGSM, we will use multivariate general linear models to examine between-group differences in average ratings of importance and feasibility across professional expertise and clusters, and we will also use χ^2^ analyses to examine differences between professions in the amount of convergence and divergence in clusters.

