Assuming that the results of the concept mapping process support the potential benefits of UCD in the implementation process, as we anticipate, this study will help expand the scope of interdisciplinary collaboration within implementation science and practice. In the future, our research team plans to explore the potential of resources (e.g. mentored development programmes) and tools (e.g. shared online workspaces) – informed by the results of this study – to support collaboration around the design of EBPs and related implementation supports. Such resources and tools would complement the limited, but growing, set of implementation training initiatives that are currently available to the field [42].

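### The team selects a cluster set by judgement for each profession and compares the two sets as results, with no masking of the profession label or common selection rule described

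*Protocol article*

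**What the plan says.** Under Participants: "We will recruit implementation science experts (*n* = 30) and UCD experts (*n* = 30) to participate in this study". The size is justified as follows: "Our planned enrolment is twice the recommended sample size for concept mapping", and the stated purpose is to allow meaningful comparison of the two groups.

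Under Analytic strategy, on how a cluster set is chosen:
- The choice of set is left to the team: "CSGM will empirically generate any number of clusters that the researcher specifies, but it is up to the researcher to select the appropriate set of" (sentence cut here).
- As an example of why, "there is no established cut-off for minimum bridge values".
- "the research team will review the results for conceptual clarity and credibility before selecting which set of clusters to report in our findings".
- Software displays guide the choice, as do outside reference points, the first being an earlier project on implementation strategies: "We will also consider the extent to which clusters are consistent with or expand upon the (1) clusters of implementation strategies identified in the ERIC" (sentence cut here). Two implementation frameworks serve likewise.

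The same section then turns to the professions: "we will apply the same analytic approach described previously with data separated by professional expertise". It lists as results the differences in number and contents of clusters and in cluster ratings. It adds multivariate general linear models for the ratings and chi-squared analyses of convergence and divergence between professions. The displays are to be produced separately for each group.

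The Discussion says that differences between the professions will be used to identify where bridging the two fields is hard.

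**The concern.** Choosing one pooled map by judgement is accepted practice in concept mapping, and the article is open about it. The difficulty starts when the choice is made twice, once per profession, and the difference between the two choices becomes a result. The number of clusters is then partly an output of the team's decision, as is the share of clusters that mix the two fields.

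If the selectors know whose map they are looking at, what strikes them as credible may differ between maps. The team includes an expert consultant for each field (Idea generation), and the named reference points come from implementation science. A selector could expect one profession's map to fit them and excuse a misfit in the other. At stake is whether a reported profession difference reflects the experts or the selectors.

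**Working it through.** **1. The plan's own figure.** The recommended minimum is 15 per group and enrolment is said to be twice that: 2 × 15 = 30 per group. This reproduces. No significance level, power, effect size or standard deviation is given, so there is no power calculation to check. The figure matters here only because the groups were sized with the profession comparison in mind.

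**2. The steps side by side.**

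| Step | What the article fixes | Who decides |
|---|---|---|
| Clusters for a given number k | Generated by the software | Data and algorithm |
| Which k, and which set, to report | Clarity, credibility, fit with prior clusters and frameworks; no cut-off | Research team |
| Repeat for each profession | Same approach on split data | Research team, twice |
| Compare number, contents, convergence | Reported as differences between professions | Follows from the two choices above |

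The fourth row inherits whatever happened in the third. Nothing described keeps the two judgements alike beyond naming the same criteria. The only concealment described is for participants: cards appear in random order with no sign of which field a strategy belongs to (Sorting and rating). Nothing comparable is described for the team's own selection.

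**3. Which results are exposed.**
- Number and contents of clusters, and convergence: fully, because they are properties of the chosen sets.
- Cluster-level ratings: only if they are computed on profession-specific clusters. The article does not say whether the general linear models use pooled or separate clusters.
- Strategy-level ratings and the pooled map: not exposed.

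**4. Illustration of the room the choice leaves.** This is not an estimate of bias from unmasked selection. Taken from the article: 36 + 30 = 66 strategies, 30 sorters per group, 5 to 20 groups per sorter. Assumed: three latent dimensions, fields shifted by −0.8 and +0.8 on one of them, sorter noise SD 0.8, classical two-dimensional scaling, Ward clustering, and a cluster counted as mixed if the minority field supplies at least 25% of it. Both groups were drawn from the same population, so there was no true difference. There were 300 replicates.
- Within one group's map, as k runs from 7 to 12, the lowest and highest shares of strategies in mixed clusters average 0.367 and 0.497. The range is 0.497 − 0.367 = 0.130, or 13 percentage points.
- With k chosen separately per group there are 6 × 6 = 36 pairs of choices. At least one pair gave chi-squared p < 0.05 in 78% of replicates, and at least one gave p ≥ 0.05 in 97%.
- With one common k = 9, p < 0.05 occurred in 29% of replicates against a nominal 5%.

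The first two results show that k alone can move the compared measure. The third shows that a common k does not validate the chi-squared test, because strategies within clusters are not independent.

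**The case against.** **The point rests partly on silence.** The article never says that the selectors know the profession. A reader might infer unmasked selection from displays made separately for each group, but that is inference, and a full protocol could contain a masking step. This stands as a limit. What remains is that the article sets out the selection procedure and its criteria in some detail, repeats it per profession, and describes no safeguard.

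**A reader might take the Discussion as showing a directional expectation.** It speaks of results that "support the potential benefits of UCD in the implementation process, as we anticipate". That expectation concerns the value of user-centred design and appears in a paragraph on future work. It states no direction for a difference between professions and could push both maps the same way. It does not support a claim of directional bias.

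**A reader might take the simulated ranges as the size of the bias.** They are not. They describe freedom in k under an assumed structure, and masked selectors would have the same freedom. No run compared masked with unmasked selection.

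**Shared constraints exist.** The same criteria and reference frameworks apply to both maps, clusters for a given k are generated empirically, and experts from both fields may balance each other. This reduces the concern but does not remove it, since the criteria leave k and the final set open.

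**The comparison is not the centre of the study.** The aims in the Background do not name a profession difference, the subgroup maps follow the pooled analysis, and the Discussion allows that further research may be needed to resolve discrepancies. That stands and lowers the weight of the point, although the groups were sized with this comparison in mind.

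**Conclusion.** The point holds in a limited form. As described, the plan lets two separate judgements by the team determine the cluster sets whose differences are then reported as differences between professions. It describes neither masking of the profession label nor a common selection rule. Differences in judgement and differences between professions are therefore confounded in the number, contents and convergence of clusters. Cluster ratings share the problem only if profession-specific clusters are used.

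No magnitude can be given: the article holds no figure from which to derive one, and the illustration does not measure the effect of unmasked selection. The conclusion assumes that the selectors can see which profession a map belongs to and that no undisclosed safeguard exists. It does not assume that the team favours any particular result. The weight is that of an optional, inexpensive improvement. The study's pooled findings stand without it.

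**What to change.** Add to the profession-comparison paragraph of Analytic strategy:

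- An existing team member who does not take part in selection produces the two profession-specific sets of candidate maps and labels them A and B.
- The team applies the same criteria, and the same candidate range of cluster numbers stated beforehand, to both.
- Both cluster sets are frozen with written reasons.
- Only then are the labels revealed and number, contents, convergence and ratings compared.

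The cost is a few sentences, relabelled output files and one member sitting out the selection. No new data, staff or participant burden is needed.

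The limits should be stated. Map content may hint at the profession, so masking may be imperfect. The cluster number remains a matter of judgement, and the chi-squared test is not made valid by masking. If the team wishes to remove the per-profession choice altogether, it could compare the professions on the pooled clusters, or directly on their co-sorting matrices with a permutation test. That is a larger change and is not needed for this point.

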### Idea generation

The first step of concept mapping involves the generation of the ideas or concepts that participants will sort and rate [32]. We completed idea generation as a research team by using existing resources that documented implementation and UCD strategies to generate a comprehensive list of 66 strategies (36 implementation, 30 UCD). The third and fourth authors served as expert consultants regarding UCD and implementation strategies, respectively, but all team members reviewed the full list of strategies. Each strategy has a short name as well as a more comprehensive, yet still brief (< 50 words), definition. Tables 1 and 2 present the full list of strategies; a list of the definitions is available from the first author upon request. After finalisation of the lists of strategies, we uploaded each strategy into CSGM as a separate ‘statement’ for subsequent sorting and rating by participants.

**Table 1 Tab1:** List and characteristics of implementation strategies generated for sorting and rating

Implementation strategy	ERIC results^a^		Primary CFIR domain(s)^b^			
	Importance	Cluster	OS	IS	ID	IN
Access new funding	3.57	F	X			
Alter incentive/allowance structures	3.17	F	X	X		
Alter patient/consumer fees	2.60	F	X	X		
Assess for readiness and identify barriers and facilitators	4.60	E	X	X	X	
Audit and provide feedback	4.40	E			X	
Build a coalition	3.77	S	X	X		
Centralise technical assistance	2.73	I	X			
Change accreditation or membership requirements	2.17	CI	X			
Change record systems	2.83	CI		X		
Conduct local consensus discussions	3.63	S		X		
Conduct ongoing training	4.17	T			X	
Create or change credentialing and/or licensure standards	2.23	CI	X			
Develop and implement tools for quality monitoring	4.37	E				X
Develop and organise quality monitoring systems	4.33	E		X		
Develop educational materials	3.80	T				X
Develop resource sharing agreements	3.07	CL	X			
Facilitate relay of clinical data to providers	4.17	CL		X		
Facilitation	4.13	I		X	X	
Fund and contract for the clinical innovation	3.67	F	X			
Identify and prepare champions	4.20	S			X	
Increase demand	3.30	CO	X			
Involve patients/consumers and family members	3.87	CO			X	
Mandate change	3.23	CI	X	X		
Obtain formal commitments	3.77	S	X			
Organise clinician implementation team meetings	3.97	S		X		
Place innovation on fee for service lists/formularies	3.40	F	X			
Promote adaptability	3.90	A				X
Provide local technical assistance	3.97	I		X		
Provide ongoing consultation	4.17	T			X	

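### Rating comparisons between professions should use the pooled cluster solution, and a difference in number of clusters should be descriptive only

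*Protocol article*

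**What the plan says.** The Analytic strategy section describes how a cluster set is reached. The software does not estimate the number of clusters but returns as many as are requested: "it is up to the researcher to select the appropriate set of clusters". The section adds that no established cut-off marks good clusters, and then: "the research team will review the results for conceptual clarity and credibility before selecting which set of clusters to report in our findings". Visual summaries and three reference points (the ERIC clusters, the CFIR domains and a third framework) guide that choice.

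The section first applies this to all participants together and rates each cluster and strategy in the resulting set. It then turns to the professions: "we will apply the same analytic approach described previously with data separated by professional expertise". On the separated data, "we will examine differences in (1) the number and contents of clusters and (2) the ratings of each cluster". The graphs are also produced separately for each group. Outside the mapping software, multivariate general linear models will examine average importance and feasibility ratings by profession and cluster. The text does not say whether the clusters in that model come from the pooled solution or from the two separate ones.

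The Participants section sets 30 experts per profession. It gives meaningful comparison between the two professions as the reason for enrolling twice the recommended minimum.

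**The concern.** The comparison between professions is a stated purpose of the study. The Discussion says that differing perspectives will be used to identify where the two disciplines are hard to bridge. A difference should therefore reflect the experts.

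**Number of clusters.** Each profession's number comes from a separate judgement by the research team. If one map is reported with, say, two more clusters than the other, the reader cannot tell whether the experts sorted more finely or the team chose a finer cut.

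**Ratings of each cluster.** The plan allows the two sets of clusters to differ in number and contents, and in the same sentence compares their ratings. Such clusters need not correspond one to one. Where they seem to correspond, they may average over different strategies. A gap between two cluster means then mixes how the strategies were rated with which strategies fell into the cluster. It can appear without any difference of opinion, or hide a real one.

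**Working it through.** **The plan's own figure.** The recommended minimum is 15 per group, and 2 × 15 = 30 per profession, as stated. No significance level, power, effect size or standard deviation is given, so no power calculation applies. The point is structural, and the arithmetic below only gives a sense of scale.

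**Number of clusters.** Let k1 and k2 be the numbers chosen for the two professions. The software returns whatever number is requested and no rule fixes the request. The reported difference k1 − k2 is therefore the difference between two team selections. The sorting data inform each selection, but nothing stated isolates their contribution.

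**Cluster ratings: inputs.** The 36 importance values and nine cluster codes in Table 1. These come from the ERIC study, not from this one, and cover implementation strategies only.

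**Formula.** A cluster of n strategies has mean m. If a strategy rated x is placed elsewhere, the mean becomes (n·m − x)/(n − 1), a shift of (m − x)/(n − 1). No rating changes.

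**Examples.**
- Provide interactive assistance (2.73, 4.13, 3.97): m = 10.83/3 = 3.61. Without the 2.73 strategy it is 8.10/2 = 4.05, a shift of 0.44.
- Adapt and tailor to context (3.90, 4.37, 3.23): m = 11.50/3 = 3.83. Without the 3.23 strategy it is 8.27/2 = 4.135, a shift of 0.30.
- Engage consumers (3.30, 3.87): m = 7.17/2 = 3.585. Without the 3.87 strategy it is 3.30, a shift of 0.285.
- Use evaluative and iterative strategies (4.60, 4.40, 4.37, 4.33, 4.40): m = 22.10/5 = 4.42. Removing the 4.60 strategy gives 17.50/4 = 4.375, a shift of 0.045, the largest in that cluster.

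**All 36 removals, one at a time.**

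| Set | Removals | Mean absolute shift | Other |
|---|---|---|---|
| All nine clusters | 36 | 4.570/36 = 0.127 | median 0.087, maximum 0.44 |
| Clusters of five or six | 21 | 1.283/21 = 0.061 | maximum 0.23 |
| Clusters of two to four | 15 | 3.287/15 = 0.219 | maximum 0.44 |

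The effect is modest in larger clusters and substantial in small ones.

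**On a common cluster set.** If both professions' ratings are averaged over the same strategies, identical strategy ratings give a difference of exactly 0 in every cluster. The artefact disappears.

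**How far membership might differ.** An illustrative simulation drew two groups of 30 sorters from one population, with 66 strategies, eight clusters imposed on both groups and identical strategy ratings. About 49% to 65% of strategies fell in matched clusters, depending on the assumed sorting noise, and matched cluster means differed by 0.16 to 0.19 on average. The simulation built in no distinct groups of strategies and let ratings vary independently of position. Both assumptions probably enlarge the result. The conclusion does not rest on it.

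**The case against.** The strongest reply concerns the general linear model. A model with profession and cluster as factors needs the same clusters in both groups, and the only single set fixed by that point is the pooled one. On that reading the main inferential rating comparison is already sound. This stands as a plausible reading. A reader might infer that the model is certain to produce spurious differences, and the document does not support that. What remains is that the text does not name the cluster set, and that the comparison of cluster ratings is stated for the separated data.

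A reader might also infer that the number of clusters is arbitrary. It is not: the choice is guided by each group's sorting data, visual summaries and existing frameworks, and the plan is open about its qualitative element. It remains a judgement rather than a measured outcome. No test of the number is planned.

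Third, 0.44 should not be read as typical. It comes from a three-strategy cluster. This study will cluster 66 strategies, with about 5 to 20 groups expected per sorter, or roughly 3 to 13 strategies each (66/20 to 66/5), so the small clusters of Table 1 may overstate the effect.

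The plan also deserves credit on two counts. Comparing cluster contents is legitimate and serves the study's aim. Go-zone graphs will already show strategy-level ratings for each profession on the same 66 items.

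Finally, a condensed article may leave the choice of cluster set to a fuller plan. That covers the model's silence, but not the comparison that the article does state.

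**Conclusion.** The concern holds in limited form. A between-profession difference in number of clusters cannot be separated from the team's two selections, and should not be interpreted as a finding about the professions. Mean ratings of separately derived clusters mix membership with opinion. In Table 1 one displaced strategy shifts a cluster mean by a median of 0.09, a mean of 0.13 and at most 0.44, and by about 0.06 on average in clusters of five or more.

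These sizes assume that one strategy moves at a time and that the earlier study's importance values are a fair guide to the spread of ratings. The structural point needs neither assumption. For the general linear model the defect is an ambiguity: there is no artefact if the pooled clusters are used. The pooled map, the comparison of contents and the separate maps as displays are unaffected. In an exploratory study this bears on how the between-profession results are read, and it should be settled before they are analysed.

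**What to change.** State in the Analytic strategy that all between-profession comparisons of ratings, including the multivariate general linear models, use the pooled cluster solution, so that each cluster holds the same strategies in both groups, and that ratings are also compared strategy by strategy. State that the separate maps, their number of clusters and their cluster ratings are descriptive displays.

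Optionally, compare sorting structure through the two 66 × 66 co-sorting matrices, with a reference distribution from permuting profession labels. This does not depend on a chosen number of clusters. Imposing the pooled number on both group maps is not required: it would set one granularity for both professions and could hide a real difference in how finely they sort.

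The cost is a change of wording and a little extra analysis. No new data are needed and the pooled solution is already produced first. The price is that group-specific cluster ratings lose any inferential role.
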